### Intervention

#### Intervention group

The intervention period will last for 12 weeks and the participants in the intervention group will perform the STS exercise, where the older person will get up from a chair to stand and then sit down again repeatedly for 1–10 times at each session depending on the participant’s ability, at least four times per day, seven days a week. The exercise will take place in conjunction with daily activities for the older person such as dressing, toileting or at transfers, and be supported by trained staff. The staff will document in a flow chart how many times per day the participant completes the activity.

The staff will be educated about the objectives of the study, and the STS exercise, at group meetings at each unit. In cooperation with the unit manager, several “key-persons” in the staff will be identified, in order to be facilitators during the intervention. The physiotherapist, occupational therapist and/or nurse working at the unit will also be asked to encourage and give practical advice to the staff regarding the STS exercise. The key-persons and representatives of the research group will meet during the intervention period. The purpose for these meetings will be to encourage the key-persons and staff to discuss problems with the intervention that might occur.

The participants will also be offered an oral protein-rich supplement (125 ml, 18 g protein which is 24% of Recommended Dietary Intake, 300 kcal) twice a day (between breakfast and lunch and in the afternoon) during 12 weeks (7 days/week). Studies indicate that only between 50 and 65% of the prescribed volume is consumed (23). Therefore, we chose a supplement with low volume and high protein content. The drink will be served in specially designed study glasses, graded in quarters. The staff will register the intake of the supplements on a flow chart designed for this purpose.

Documentation of the daily exercises and nutritional supplements will be checked every week by the key-persons.

#### Harms

Solicited and spontaneously reported adverse events and other unintended effects of the trial interventions will be collected and reported by the ward nurses at the NH units.

#### Control group

The participants in the control group will receive standard care only and no extra intervention.

### Data collection/outcomes

The quantitative data will be collected at baseline and at the 12-week follow-up. An overview of the data collection is presented in Table 1. The following assessments will be performed to follow variables related to the primary and secondary aims for the study:

**Table 1 Tab1:** Participant timeline

	Enrollment	Allocation	Postallocation		
TIMEPOINT	*-t* _*1*_	0	*t* _*1*_ *baseline*	*t* _*2*_ *intervention*	*t* _*3*_ *w 13*
ENROLLMENT:					
*Eligibility screen*	X				
*Informed consent*	X				
*Information to staff and next of kin*	X				
*Identification of* *“key-persons” and meetings together with representatives from the research group*		X	X	X	X
Allocation		X			
INTERVENTIONS:					
*Sit-to-stand*				X	
*Oral supplementation*				X	
ASSESSMENTS:					
*Sit-to-stand*			X		X
*Functional balance*			X		X
*Walking ability*			X		X
*ADL*			X		X
*Nutritional status*			X	X subgroup	X
*Health related quality of life*			X		X
*Healthcare resource use*			X		X
*Demographic data*			X		
*Medical incidences*				X	X
*Interviews of residents*					X
*Interviews of staff*				X	X

t_1_ baseline, t_2_ intervention period of 12 weeks, t_3_ 12 weeks follow up

#### Primary outcome

The number of chair rises in 30 s [30] will be the primary outcome for the study.

#### Secondary outcomes

##### Physical function

Functional balance will be measured by the Berg Balance scale [31, 32]. The scale consists of 14 tasks of relevance for everyday life and each item scored from 0 to 4, maximum score of 56. Walking speed will be measured (in participants who can walk) by walking propulsion indoors for a distance of 10 m at self-selected speed [33]. ADL will be measured with Functional Independence Measure which comprises 18 items grouped in the following functional domains: bathing, bowel management, toileting, eating, dressing lower body and social interaction [34, 35]. It is scored on a 7-point scale from 1 (dependent) to 7 (independent).

##### Nutritional status

Mini Nutritional Assessment-Short Form (MNA-SF) will be performed [36]. MNA-SF is scored 0–14 points. It includes six parts: evaluating decline in food intake, weight loss, mobility, physiological stress or acute disease, cognitive condition and BMI or calf circumference. 12–14 = normal nutritional status; 8–11 = at risk for malnutrition; 0–7 = malnourished. Food intake will be registered 2 consecutive days at baseline, at 6- and 12-week follow-up in a subgroup (25%) of the participants in the intervention group. Blood chemistry: Plasma albumin, plasma transthyretin, plasma C-reactive protein (CRP) to determine any active inflammatory process. Further the anabolic mediator plasma insuline-like growth factor-1 (IGF-I) and D-vitamin status will be assessed by S-25 (OH) vitamin D. Body composition measurements: Bioelectrical impedance analysis (BIA) [37].

*Quality of life* will be assessed using the EQ5D-5 L [38], a questionnaire comprising 5 questions corresponding to 5 health domains: pain, mood, mobility, self-care and daily activities. Each question has 5 levels: level one = no problems, level two, three and four = some, moderate or pronounced problems and level five = extreme problems. The participants’ opinion of their own health today, is valued according to a visual analogue scale. The scale is ranged from 0 = worst imaginable health state, to 100 = best imaginable health state.

*Healthcare Resource Use* data will be assessed by The Resource Utilization in Dementia (RUD©) [39] on the key cost components including: time of the healthcare assistant for personal ADL, hospitalizations (including length of stay), the number of visits to different types of healthcare professionals (both as outpatients and as a home visit), use of lifts.

##### Medical incidences

The effects of the intervention on frequency and incidence of falls, pressure ulcers and incontinence will be assessed from patient records and study documents at baseline and at the 12-weeks follow-up. Falls: Falls documented by health care professionals in patient records will be monitored to assess the safety of the intervention and the effects on incidence of falls. Pressure ulcers: Information on the occurrence of pressure ulcers will be obtained from the patient health record. Mobility related to toilet habits: Mobility status related to toilet habits will be recorded; whether the participant is self-reliant; needs supervision or some help; or is totally dependent on help. Information on this data will be recorded in a specific document for the study.

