### Objectives

The main hypothesis of the OPEN study is that physical exercise performed as a daily routine along with a protein supplement, will result in improved physical function status and independence in everyday life activities and thereby enhance health-related quality of life in older persons living in nursing homes.

Specific aims of the study are:*Aim I:* To investigate the effects of the STS exercise combined with an oral protein-rich supplement on physical function and nutritional status, and health-related quality of life, and the frequency and incidence of falls, pressure ulcers and incontinence in older nursing home residents.*Aim II:* To estimate the cost effectiveness of the combination of the STS exercise and oral protein-rich supplement vs. the control group.*Aim III:* To describe the residents’ perceptions and experiences of daily being offered to conduct the STS exercise and to drink the nutritional supplement.*Aim VI:* To describe nursing home staff’s experiences of supporting the STS exercise and to offer the nutritional supplement to residents.

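### Incontinence is a named Aim I outcome, but the variable described in its place is help needed with toilet mobility, which is not continence

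*Protocol article*

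**What the plan says.** Aim I, under Objectives in the protocol article, includes effects on "the frequency and incidence of falls, pressure ulcers and incontinence in older nursing home residents". The Medical incidences section repeats this as an outcome: "The effects of the intervention on frequency and incidence of falls, pressure ulcers and incontinence will be assessed from patient records and study documents". It places the assessment at baseline and at 12 weeks.

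The section then gives one short description per item. Falls are those that professionals document in patient records. Pressure ulcers are occurrences taken from the health record. The third description reads: "Mobility status related to toilet habits will be recorded; whether the participant is self-reliant; needs supervision or some help; or is totally dependent on help". On where this is captured, the section adds: "Information on this data will be recorded in a specific document for the study". Incontinence is not mentioned again in the section.

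One other continence-related item appears. Under Physical function, the Functional Independence Measure is the ADL instrument, and its domains are listed as "bathing, bowel management, toileting, eating, dressing lower body and social interaction", each item scored 1 to 7. In Table 1 the ADL row is marked at baseline (t1) and follow-up (t3). The row "Medical incidences" is marked at t2 and t3 only.

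**The concern.** The outcome that is promised and the variable that is described are different constructs. Needing help to get to the toilet is a matter of mobility, whereas continence is a matter of bladder and bowel control. A self-reliant resident can be incontinent, and a resident who needs full help can be continent.

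The article itself keeps the two apart. Its Background presents impaired mobility as something that raises the risk of incontinence, that is, as cause and consequence. Letting the toileting rating stand for incontinence would replace the outcome with its presumed mediator.

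The direction of a possible error also matters. The Intervention section integrates the exercise into dressing, toileting and transfers with staff support, so the toileting rating lies close to the trained activity. The Blinding section accepts that masking the assessors is hard to achieve. An improved toileting rating is thus a likely finding. If no continence data sit beside it, it could be reported under an aim that speaks of incontinence.

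**Working it through.** No arithmetic applies. The article's only sample-size figure (49 per group, 60 after attrition) concerns chair rises and has no bearing here. The check is to set each promised outcome beside what is described for it, and then to search the other outcome sections for a measure of continence.

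**1. Promised against described**

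| Outcome named in Aim I | Description under Medical incidences | Same construct? |
|---|---|---|
| Falls | Falls documented in patient records | Yes |
| Pressure ulcers | Occurrence, from the health record | Yes |
| Incontinence | Three-level help needed with toilet-related mobility | No |

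**2. Can the rating be converted into continence?** Three levels of help crossed with continent or incontinent give 3 × 2 = 6 combinations, all of them possible. Knowing how an arm of 60 residents divides over the three levels places no bound on how many are incontinent: the number could be anything from 0 to 60. The rating therefore supplies neither a frequency nor an incidence of incontinence.

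**3. Other candidate measures**
- *Patient records and study documents.* These are named as sources for all three outcomes. For incontinence no variable is attached to them. The one item that the section assigns to a study-specific document is the toileting rating.
- *Functional Independence Measure.* Bowel management is among the listed domains. It is specified for ADL, is not linked to the incontinence aim, and is a 1-to-7 dependence score rather than an event or a status. No bladder item is listed. The article does not list the 18 items one by one, so it does not show whether bladder control is among them.
- *The other outcomes and sample characteristics* (balance, walking speed, nutritional status, EQ-5D, resource use, cognition, sarcopenia, frailty) include none that is described as recording continence.

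**4. Timing.** The text says "falls, pressure ulcers and incontinence will be assessed from patient records and study documents at baseline and at the 12-weeks follow-up". Table 1 marks these outcomes at t2 and t3, with nothing at t1, while the rows for physical function, ADL, nutrition and quality of life all carry a t1 mark. For incontinence and pressure ulcers, which persist, incidence means onset in a resident who did not have the condition at baseline, so baseline status is needed. For falls, which are discrete events, a count over follow-up suffices.

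**The case against.** The best defence is that this is a condensed article. It points to study documents that are not shown, and details such as type of incontinence, categories or pad use belong on a case report form. Pressure ulcers are also described briefly, without grade or counting rule. The toileting variable is labelled as mobility, and nowhere does the text equate it with incontinence.

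Much of this stands. The absence of categories or counting rules would be no finding by itself, and it is not certain that the toileting rating would be reported as incontinence. What does not fall away is the substitution. The article does not merely stay brief on incontinence. It gives a specific variable with its levels in the place where incontinence should be, and that variable measures something else. Pressure ulcers, however briefly treated, are at least described as pressure ulcers.

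A reader might go further and infer that toileting help is the only measure available and that an effect on incontinence cannot be estimated. The documents do not support that. Records are a named source and may hold continence data, and bowel-management scores could be compared between arms.

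A reader might also infer from Table 1 that baseline status goes uncollected, so that incidence is out of reach for all three outcomes. That too goes beyond the documents. The Medical incidences text states a baseline assessment, and the opening of Data collection/outcomes says that quantitative data are collected at baseline and at 12 weeks. The missing mark is a discrepancy between table and text, and for falls it would not matter.

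**Conclusion.** The concern holds as a mismatch between a stated aim and its described measurement. One of the three clinical outcomes named in Aim I has no operational definition, and the variable in its place is toileting dependence. Followed as written, the plan may end without a usable incontinence result, or with a mobility result placed under the incontinence aim. Separately, Table 1 and the text disagree on whether these outcomes are taken at baseline. This matters for incontinence and pressure ulcers, but not for counting falls.

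The reach is limited. This is a secondary outcome, and the primary outcome, the sample size and the mixed-model analysis are untouched. It is still worth correcting, because continence at baseline cannot be recovered later unless the records happen to hold it.

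The conclusion assumes that the study-specific document records what the article says it records. If that form already has a continence field, only the article's wording and Table 1 need correction.

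**What to change.** 1. Add continence status, urinary and faecal, to the existing study document at t1 and t3, and name it in the Medical incidences section as the incontinence outcome. Use the bowel-management item of the Functional Independence Measure as support.
2. Keep the toileting rating, but list and report it as a separate mobility outcome under its own name.
3. If continence will not be recorded, rename the outcome as toileting dependence in both Objectives and Medical incidences. This costs nothing in data collection but gives up the incontinence part of Aim I.
4. Reconcile the Medical incidences row of Table 1 with the text on baseline assessment, so that new incontinence and new pressure ulcers can be separated from those already present.

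The cost of the first option is one or two form fields and a few minutes of staff time per resident. New incontinence can be counted only among residents continent at baseline. The article gives no prevalence, so the size of that group is unknown and the estimate may be imprecise.

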#### Sample characterization

*Demographic data* on age, sex, and medical diagnosis will be collected and described. *Cognitive function* will be assessed using Mini Mental State Examination (MMSE; 0-30p) [40]. *Sarcopenia* will be assessed according to the recommendation of EWGSOP [14] by SARC-F questionnaire [41] and *frailty* will be assessed by the Frail questionnaire screening tool [42].

### Sample size calculation

The sample size calculation for the number of participants is based on the effect size of the primary outcome measure in a pilot study performed and described in a study protocol by a Canadian research group that we collaborate with [24]: that is the number of sit-to-stands that the participant is able to complete in 30 s. An increase of 2 sit-to-stands completed in 30 s is suggested to be a meaningful change in the person’s mobility. Based on existing research [30, 43–45] the standard deviation of the 30-s sit-to-stand measure is 3.5 sit-to-stands. Based on the power calculation by Slaugther and colleagues [24], 49 participants in each group are needed to detect an increase in the number of sit-to-stands (power = 0.80; 2-tailed; α = 0.05). Assuming an attrition of 20% over the 12 weeks, we will recruit in total 120 participants (60 participants to each group).

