## Methods

### Trial design

This study protocol has been informed by the SPIRIT guidelines [28]. The study is a two-arm cluster-randomized controlled trial which will be performed in NH at two municipalities in the Stockholm area. There are in total 62 NH units (34 dementia care, 28 somatic care; approx. 571 beds). A cluster will be defined as a group of 1–3 NH units with in total approximately 15–38 persons depending on the size of a unit. The clusters will be randomized according to a computer based sample list into two groups; intervention group and control group. The cluster design is chosen to prevent spread of the STS exercise to the control groups. This study has been registered with the number protocol of ClinicalTrials.gov Identifier: NCT02702037. An overview of the study is presented in Fig. 1.

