### Data analyses

All data will be entered into a database using SPSS (iBM). Quality controls will be made to check that the data are entered correctly. The baseline characteristics of the participants in the intervention and control groups will be compared using descriptive statistics. All analysis will be done by members of the research group and by an independent statistician respectively.

Data for primary and secondary outcome measures will be analysed using descriptive and comparative statistical analyses including multi-level statistics appropriate for the data measurement levels and data distributions. Data will be analysed according to intention-to-treat, i.e. participants who will drop out before completing the 12 weeks of follow up will be included in the data analysis. The model of data analysis needs to consider the effect of clustering. Thus, this study will use mixed effect models with the cluster treated as a random effect.

Combining the resource units with the cost price will allow the calculation of total costs of each group. The cost effectiveness calculation will use the EQ5D-5 L as outcome. Costs and effects will be examined based on the principle of cost-consequence analysis. This type of analysis lists all relevant costs and effects (consequences) in order to capture as much information as is feasible, in order to allow decision makers to choose the outcome of interest for inclusion in economic analyses [54].

The qualitative data consisting of tape-recorded interview-answers will be transcribed verbatim. The qualitative data sets will be analysed from a data-driven inductive approach. More specifically, the transcripts of the interviews will be read and analysed using a constant comparative method described by [29].

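### The 49 per group assumes independent residents and the step to 60 covers only attrition, so the stated 80% power is not supported for a cluster-randomised trial

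*Protocol article*

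**What the plan says.** Under Trial design, the protocol article describes a two-arm cluster-randomised trial: "The clusters will be randomized according to a computer based sample list into two groups". It adds: "A cluster will be defined as a group of 1–3 NH units with in total approximately 15–38 persons depending on the size of a unit". Also in that section, the source population is given as 62 units with about 571 beds.

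Under Sample size calculation, a change of 2 chair rises in 30 seconds is taken as meaningful and the SD as 3.5. From a Canadian group's power calculation the article adopts the figure "49 participants in each group are needed to detect an increase in the number of sit-to-stands", with power 0.80, two-sided, alpha 0.05. The only further step is for dropout: "Assuming an attrition of 20% over the 12 weeks, we will recruit in total 120 participants", which makes 60 per group.

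Under Data analyses, the article says "The model of data analysis needs to consider the effect of clustering" and plans a mixed model in which cluster is a random effect.

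**The concern.** The analysis and the sample size treat the residents differently. The planned model lets outcomes within a cluster be correlated, and that widens the standard error of the treatment difference. The sample size appears to assume that this correlation is zero. If so, 0.80 is the power of a different trial, one that randomises individual residents.

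The power figure colours how a non-significant primary result is read. A reader who takes 0.80 at face value may treat such a result as good evidence against a 2-rise effect when the trial was less able to detect one than stated.

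**Working it through.** **Inputs from the protocol article.** Difference 2, SD 3.5, two-sided alpha 0.05, power 0.80, 49 per group, 20% attrition, 60 per group recruited (Sample size calculation). Clusters of about 15–38 persons and about 571 beds (Trial design).

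**Step 1: reproduce 49.** For two independent samples, n per group = 2 × [SD × (1.960 + 0.842) / difference]² = 2 × [3.5 × 2.802 / 2]² = 48.07, rounded up to 49. This matches the stated figure. A t test with 49 per group has power 0.80. No inflation for clustering is contained in 49.

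**Step 2: what the step to 60 buys.** 60 × 0.8 = 48 evaluable per group. Power at 48 without clustering is 0.79 by the t test (0.799 by the normal formula). Attrition uses up the whole margin.

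**Step 3: range of cluster numbers (assumed).** If all 571 beds were grouped into clusters of 38 or of 15, there would be 571/38 ≈ 15 to 571/15 ≈ 38 clusters. With 120 residents that is about 8 down to 3 enrolled per cluster. I use 38 and 16 clusters, and 8 as an extreme case.

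**Step 4: power with clustering.** Let k be the number of clusters. Analysed residents per cluster are m = 96/k, the design effect is DE = 1 + (m − 1) × ICC, and the effective number per arm is 48/DE. Power comes from the noncentral t distribution with noncentrality 2 / [3.5 × √(2·DE/48)]. The degrees of freedom are either those of a two-sample t test on the effective numbers (large df) or k − 2.

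Example with 16 clusters and ICC 0.05: m = 6, DE = 1 + 5 × 0.05 = 1.25, effective n = 48/1.25 = 38.4, standard error = 3.5 × √(2/38.4) = 0.799, noncentrality = 2/0.799 = 2.50. Power is 0.70 (large df) or 0.64 (14 df).

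| Clusters | m | Power at ICC 0.01 / 0.05 / 0.10, large df | Same, k − 2 df |
|---|---|---|---|
| 38 | 2.5 | 0.79 / 0.76 / 0.73 | 0.77 / 0.75 / 0.72 |
| 16 | 6 | 0.77 / 0.70 / 0.61 | 0.72 / 0.64 / 0.57 |
| 8 (extreme) | 12 | 0.75 / 0.60 / 0.47 | 0.60 / 0.47 / 0.37 |

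**Step 5: difference detectable with 80% power at ICC 0.05.** This is approximately (t for 0.975 + t for 0.80) × standard error.

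- 16 clusters, standard error 0.799: 2.83 × 0.799 ≈ 2.3 on 94 df; 3.01 × 0.799 ≈ 2.4 on 14 df.
- 8 clusters, DE = 1 + 11 × 0.05 = 1.55, standard error 3.5 × √(2 × 1.55/48) = 0.889: 2.83 × 0.889 ≈ 2.5 on 94 df; about 3.0 on 6 df.

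**The case against.** Several points can be made for the plan.

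- **The ICC and number of clusters may be in a fuller document.** This stands as far as it goes: their absence from a journal article is not the fault. But a later ICC cannot make 49 cluster-adjusted, and the article fixes recruitment at 60 per group.
- **The figure comes from another group's calculation.** The article adopts it as this trial's requirement, and it reproduces only with a design effect of 1.
- **The mixed model deals with clustering.** It protects the error rate of the test. It does not supply the missing information.
- **Intention to treat keeps all 60.** With 60 analysed per arm, power would be about 0.88 at ICC 0, and 80% would hold up to DE = 60/48.07 ≈ 1.25 (ICC about 0.035 at m = 8, about 0.12 at m = 3). But the outcome is measured only at baseline and 12 weeks, so residents without a 12-week value add little. The plan itself budgets for 20% loss.
- **Baseline adjustment could restore the power.** This is the strongest point. If adjustment multiplies the variance by (1 − r²), then at ICC 0.05 and an assumed r = 0.5, large-df power is about 0.87 (38 clusters), 0.82 (16) and 0.73 (8). At r = 0.6 it is 0.92, 0.87 and 0.79. The article neither states such an adjustment nor uses it in the calculation, so it cannot be credited yet.

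A reader might go further and infer that the trial is certainly and badly underpowered. The documents do not support that. With many small clusters and a low ICC the loss is about one percentage point, and an adjusted analysis might exceed 80%. Nor should the 15–38 persons be used as m. They are the residents living in a cluster, and 120 of 571 is only 21% of beds. The 8-cluster row is extreme for the same reason: eight clusters hold 120 to 304 persons, so 120 participants would mean enrolling 39% to 100% of them.

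**Conclusion.** The sample size statement is wrong as written. Both 49 and 60 are figures for individually randomised residents, and on the stated inputs any positive ICC leaves power below the claimed 0.80. That conclusion needs no assumed value.

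The size of the shortfall does need assumptions on ICC and number of clusters. It ranges from negligible (0.79 with 38 clusters at ICC 0.01) to substantial (0.61 with 16 clusters at ICC 0.10, or 0.57 on 14 df). At ICC 0.05 the detectable difference is about 2.3 to 2.5 rises on a large-df basis for 16 down to 8 clusters, or 2.4 to 3.0 on clusters minus 2 df, rather than 2. These figures take equal cluster sizes and no baseline adjustment. The supportable claim is that the calculation does not justify 80% power, not that the trial cannot reach it.

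**What to change.** Keep the 120 residents and correct the claim. In the sample size section:

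1. State that 49 per arm assumes independent residents.
2. Give the planned number of clusters and an ICC range, for example 0.01 to 0.10.
3. Restate power and the difference detectable with 80% power for 48 evaluable per arm, using 1 + (m − 1) × ICC with m the analysed residents per cluster. Name the degrees of freedom, and use the same basis for both quantities.
4. Credit baseline adjustment only if the primary model prespecifies it and the assumed baseline-to-follow-up correlation is stated.

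The cost is a rewritten paragraph and, unless a prespecified adjustment makes up the loss, a less favourable stated power. No extra residents are needed.
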